#### Component 2: stakeholder perspectives: patients, relatives, and staff

This component of the study will use qualitative methods to describe how the redesigned ICU bedspaces influence the patient experience in ICU from the perspective of patients, family members, and staff. Patients admitted to the intervention bedspaces who survive their ICU admission will be invited to take part. Data will be collected in semi-structured interviews with individual patients, accompanied by family members when available and willing to take part. Interviews will be conducted within a week after discharge from ICU but before hospital discharge. Staff from medical, nursing, allied health disciplines, and non-clinical/operational staff providing a range of services in the ICU will be invited to participate in focus groups or individual interviews. The interviewer will use a topic guide flexibly to explore participants’ experiences in the intervention bedspaces. Based on our previously conducted baseline studies [4, 31], we anticipate that between 10–15 patients and 25–30 staff will be required to reach saturation and address research questions.

The approach to analysis of the qualitative interviews has been described in detail elsewhere [4, 31]. In brief, recorded interviews will be transcribed and analysed using a framework approach [35]. Framework analysis consists of five steps: (1) familiarisation, (2) identifying thematic framework, (3) indexing, (4) charting, and (5) mapping and interpretation.

#### Component 3: sleep quality and quantity

The quality and quantity of participants’ sleep will be measured objectively, using a combination of single forehead sensor electroencephalogram (EEG) and polysomnography, as well as subjectively using validated sleep questionnaires. Sleep studies will only be commenced when the effects of relevant medications are no longer likely to impact on the quality of data collected; therefore, sleep will not be measured on participants that are deeply or moderately sedated (RASS score − 3, − 4, or − 5), or have had a general anaesthetic, drug overdose, or alcohol intoxication in the preceding 24 h. Ventilated and non-ventilated participants will be included.

Sleep will be measured continuously for a 2–4-day study period (dependent on duration of ICU admission) following recruitment using the Somfit single forehead sensor EEG (Compumedics®). This is a recently developed wearable device that is light and comfortable for patients to wear while enabling collection of high-quality EEG signals.

Sleep will be concurrently measured using a gold-standard portable polysomnography (PSG) recorder for a 24-h period. Polysomnography involves the application of sensors and electrodes for the continuous monitoring of physiological variables during sleep. The portable PSG is a small device that is worn as a belt across the patient’s thorax. Ten sensors are attached to the patient: 2 under the chin, 1 next to each eye, and 6 on the scalp. The sensors will measure and monitor muscle tone changes using electromyogram (EMG), eye movements using electrooculogram, and electrical activity in the brain using EEG. The equipment also has an inbuilt oximeter to measure pulse oximetry and can also measure patient body position as well as background light and sound. The equipment also collects electrocardiogram, leg EMG, nasal pressure/thermistor, and ribcage/abdominal movements.

Participants will be asked to complete the validated sleep in the ICU questionnaire and the Morningness-Eveningness Questionnaire before discharge from ICU [36, 37]. The aim of these questionnaires is to establish the patients’ reported quality and quantity of sleep as well as the reasons for sleep disruptions.

The data will be analysed and interpreted by expert sleep scientists. Objective measures of sleep will be described for a minimum 24-h period, including total sleep time, time awake, sleep staging (stage 1 and 2, slow wave sleep, and rapid eye movement (REM) sleep), arousal index, number of awakenings across the 24-h period, and percentage of sleep at night-time versus daytime hours. Objective sleep quality will be compared between control and interventional beds.

#### Component 4: circadian rhythms

For this component, data will be collected from environmental sensors, study records, participants, medical records, and biological samples. The following measured variables will be analysed to evaluate the circadian synchronisation of the patients and study their influence on the outcome of the patients:

Routinely collected physiological data, including body temperature, heart rate and heart rate variability, blood pressure, pulse oximetry, and enteral/parenteral feeding rhythmRelevant medications with the potential to modify patients’ heart rate and blood pressureQuality and quantity of sleep (as described for component 3 above)Four-hourly blood samples for 48 h, specifically looking at cortisol, melatonin, insulin-like growth factor 1, inflammatory markers (full blood count and c-reactive protein), haemoglobin, proteomics analysis, and expression of circadian clock genes and untargeted RNA-sequencing in white blood cells

Biological measured variables will be assessed using a modified version of dryR, a statistical framework to assess differential rhythmicity [38]. The analysis is based on multiple mixed linear regression with a subsequent model selection approach based on the Bayesian information criterion to assess differential rhythmicity of the measured variables, comparing patients admitted to the intervention versus control beds. The mixed linear models will include fixed effects from a harmonic regression model and a random effect (patient–specific) on the intercept that deals with the subject–to–subject variation and dependency of the repeated measures. Rhythmic parameters including amplitude and acrophase will be computed from the selected model for each of the conditions. This will identify circadian/diurnal variables that are impacted by the intervention.

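### Circadian model: a random intercept covers only mean level, so the uncertainty of the rhythm parameters compared between arms is understated if patients differ in phase or amplitude

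*Protocol article*

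**What the plan says.** The section on Component 4 (circadian rhythms) of the protocol article fixes the following.

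- Sampling: "Four-hourly blood samples for 48 h", with assays that include "proteomics analysis, and expression of circadian clock genes and untargeted RNA-sequencing in white blood cells".
- Mean structure: "The mixed linear models will include fixed effects from a harmonic regression model".
- Random structure: one term per patient, described as "a random effect (patient–specific) on the intercept that deals with the subject–to–subject variation and dependency of the repeated measures". The section describes no other modification of the dryR framework and names no random effect on the harmonic terms.
- Decision rule: a "model selection approach based on the Bayesian information criterion to assess differential rhythmicity of the measured variables".
- Contrast: between the two types of bedspace, that is, between different patients.
- Estimates: "Rhythmic parameters including amplitude and acrophase will be computed from the selected model for each of the conditions", so per arm and not per patient.
- Interpretation: "This will identify circadian/diurnal variables that are impacted by the intervention".

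**The concern.** The article states the model and a reason for it, so this is a stated rule and not a detail left to the full protocol or an SAP. The reason does not fit the parameters of interest. A patient-specific intercept lets patients differ in their 24-hour mean. Amplitude and acrophase are functions of the cosine and sine coefficients, and the model gives every patient in an arm the same pair. If patients in fact differ in timing or strength of rhythm, their repeated samples remain correlated through those coefficients and the model ignores it.

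Two things are at stake. First, rhythmic variables can be labelled as affected by the bedspace when the arms differ only by chance in which patients they contain. Such labels would carry into the planned analysis, in the section on data collection and analysis, that relates circadian maintenance to post-intensive care syndrome. Second, a group-mean harmonic becomes smaller when patients are out of phase with each other, so an arm's reported amplitude mixes individual rhythm strength with scatter in timing.

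**Working it through.** **Inputs from the article.** The section on recruitment expects about 250 randomised, about 50 ineligible and 50% declining: (250 − 50) × 0.50 = 100 patients, which reproduces its figure. Allocation is 1:1, so at most about 50 per arm. Samples per patient: 48 / 4 = 12 (13 if both ends are counted; 12 used). No error rate, power, between-patient spread or signal-to-noise ratio is given for this component, so there is no such figure to reproduce.

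**Assumed, shown as a range.** Phase SD of 0, 2 or 4 h, or fully random phases; amplitude CV 0 to 0.5; amplitude A of 0.5, 1 or 2 residual SDs (σ).

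**Mechanism by hand.** Twelve equally spaced samples cover two full cycles, so the squared cosine terms sum to 6, as do the squared sine terms. If each coefficient varies between patients with variance τ², then, per patient:

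- actual variance of an estimated coefficient: τ² + σ²/6;
- variance the random-intercept model works with: (σ² + 12τ²/11)/6, because the spread adds 12τ² to the within-patient sum of squares on 11 degrees of freedom.

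With τ² = 0 both equal σ²/6 and the model is right. With random phases and a common amplitude, τ² = A²/2:

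- A = σ: actual 0.5 + 0.167 = 0.667; model (1 + 0.545)/6 = 0.258; ratio 2.6.
- A = 2σ: actual 2 + 0.167 = 2.167; model (1 + 2.182)/6 = 0.530; ratio 4.1.

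**Effect on BIC selection.** Simulation under the null (5,000–10,000 trials per setting), with both arms drawing patients from one distribution. Five candidate models: no rhythm, rhythm in one arm only (two models), same rhythm, different rhythms. The lowest BIC is chosen. A false differential selection is either one-arm model or the different-rhythms model. Results for 50 per arm, BIC penalty on observations:

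| Phase spread; amplitude CV | A = 0.5σ | A = σ | A = 2σ |
|---|---|---|---|
| none; 0 | 0.04% | 0.02% | 0.08% |
| SD 2 h; 0.3 | 0.2% | 1.7% | 8.2% |
| SD 4 h; 0.5 | 3.7% | 6.0% | 17.0% |
| random phases | 2.3% | 12.9% | 28.4% |

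- Separate runs gave about 2% and 9.5% for SD 2 h at A = σ and A = 2σ. With a circular phase SD of about 4.9 h, CV 0.3 and A = σ, they gave 7% at 50 per arm, 14–16% at 25 and 23–24% at 15.
- Fewer patients make it worse. At SD 4 h, CV 0.5 and A = 2σ, the rate is 17.0%, 20.6% and 30.6% with 50, 25 and 10 per arm.
- With the BIC penalty on patients, the rate at 50 per arm is about 1% for homogeneous patients and 2% to 46% otherwise.
- Variables with no rhythm: about 0.1–0.5%.
- The closed-form fit agreed with a standard mixed-model routine in one setting: 20.6% against 20% in 60 runs.

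**With patient-level random cosine and sine terms** (50 per arm, A = 2σ, penalty on observations): 8.2% falls to 0.1%, 17.0% to 0.1% and 28.4% to 0.2%. Where the mean rhythm is weak, less is removed: 3.7% falls only to 2.9% (SD 4 h, CV 0.5, A = 0.5σ). There much of the error comes from BIC choosing a one-arm model over the same-rhythm model.

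**Amplitude shrinkage.** For normally distributed phases with SD s hours, the group amplitude is the individual amplitude times exp(−(2πs/24)²/2). For s = 2 this is exp(−0.137) = 0.87; for s = 4, exp(−0.548) = 0.58.

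**The case against.** The strongest reply is that the size is unknown. The article gives neither between-patient spread nor signal-to-noise ratio, and with 50 per arm, small spread and a weak rhythm the false rate is only about 0.2%. The component is one of seven, in a study that says no power calculation was possible, and no treatment decision hangs on it. All of this stands and limits the claim about size. It does not rescue the sentence on what the intercept achieves.

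A reader might go further in four ways that the documents do not support.

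- **That the arm estimates are biased.** They are not. With randomised arms, the group cosine and sine coefficients estimate the group-mean harmonic without bias; their stated precision is what is wrong.
- **That a false-selection rate can be multiplied by the number of proteins and transcripts.** A variable with no rhythm has no phase or amplitude spread for the model to mishandle. The count depends on the share of rhythmic variables, which is not given.
- **That the size of a 5% test describes the plan.** The article uses BIC and states no alpha, and no smaller blood-sampling subset either. The rates below 50 per arm show sensitivity, not the planned design.
- **That multiplicity over the omics variables is neglected.** A condensed article may leave that to the full protocol or SAP.

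It can also be argued that a group rhythm which weakens when patients are desynchronised is informative, since the section sets out to evaluate patients' circadian synchronisation. That is fair, but only if loss of individual rhythm and scatter between patients are reported separately.

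**Conclusion.** The point holds as a fault in a stated rule. The random intercept deals with differences in mean level and not with dependency in the coefficients being compared. If patients differ in phase or amplitude, uncertainty is understated and differential rhythms are selected too often among rhythmic variables. The direction was the same in every heterogeneous setting tried. The size is conditional on the assumed spread, signal-to-noise ratio and BIC penalty, and on about 50 per arm being sampled: it can be negligible or exceed a quarter of null rhythmic variables. If patients are homogeneous, the model as written is sound. Confidence is high for the mechanism and low for any single rate. The change should be made, but it concerns one component's analysis and not the trial as a whole.

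**What to change.** Replace the random-intercept specification by one of the following:

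1. keep the harmonic mixed model and add patient-level random effects on the cosine and sine terms, with their covariance estimated; or
2. fit a cosinor to each patient and compare the coefficient pairs between arms, for example with Hotelling's test. In the simulations this test held about 5% at a nominal 5%.

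Reword the justification so that the intercept is credited only with differences in mean level.

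Separately, report per-patient amplitude and between-patient phase dispersion by arm. Neither option alone changes the shrinkage of the group-mean harmonic, because both still compare mean coefficients.

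The cost is wording and code, with no new data or visits. Intervals will be wider and fewer variables will be called differential. If very few patients per arm are sampled, some false selection remains: with 10 per arm, phase SD 4 h, amplitude CV 0.5 and amplitude 2σ, random harmonic terms reduce it from about 31% to about 8%, not to zero.

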#### Component 5: delirium prevalence

The prevalence of delirium will be assessed by the completion of the confusion assessment method for the intensive care unit (CAM-ICU) twice per day (morning and afternoon) for all enrolled patients by a member of the research team.

Delirium data analysis will involve:

The prevalence and incidence of delirium will be calculated and compared between intervention and control bedspaces.Comparison of cases and non-cases on demographic and diagnostic data and length of stay will be undertaken using methods appropriate to type of data: T-tests, chi square, and ANOVA.

For this study, a case of PICS will be defined as any participant with questionnaire scores outside of normal ranges indicating impaired physical (EQ-5D-5L), psychological (HADS or PCL-5), and/or cognitive function (PROMIS). The incidence of PICS will be described using proportions and associated 95% confidence intervals and compared between sub-populations, such as ICU stay < 48 h, planned vs. emergent admission, ventilated vs. non-ventilated, and type of bedspace admitted to. Multivariable regression analysis will be used to identify factors associated with PICS, or not getting PICS. The overall characteristics of the sample will be described using summary statistics. This will help inform the generalisability of our results. The number of patients approached and consented will be tabulated, together with the number who were lost to follow-up, withdrew from the study, or died.

#### Component 7: health economic evaluation

A within-trial cost-effectiveness analysis will be conducted to estimate the changes to total costs and patient outcomes associated with the intervention. The change to total costs will reflect the cost of implementing the intervention under different scenarios, offset by the economic value of ICU bed days saved from reduced ICU length of stay [43]. Planned scenarios will consider different definitions of implementation costs per intervention bedspace, which will impact the change in total costs per unit of health benefit. Definitions will reflect the cost of maintaining a bedspace that already exists in the ICU (base case), the cost of adding a new bedspace within an existing ICU, and the cost of building a new ICU to accommodate the intervention. These costs will be measured from the health system perspective. We will further consider the economic value of lost productivity from the patient perspective, which will be collected using the patient employment information questionnaire. Patient outcomes will be measured in quality-adjusted life years, which reflect patient life expectancy adjusted for health-related quality of life. Life years will be estimated using Australian life tables based on patients’ sex and age at the time of ICU admission. Quality of life, measured under component 6 via the EQ-5D-5L, will be used to estimate health utility values needed to convert life years to quality-adjusted life years.

Cost-effectiveness outcomes will be reported as an incremental cost-effectiveness ratio and net monetary benefit, for different willingness to pay thresholds. The impact of model input uncertainty on cost-effectiveness outcomes will be examined by deterministic sensitivity analysis and probabilistic sensitivity analysis. Model input distributions needed to conduct sensitivity analyses will be informed by available study data, published literature, and expert opinion where appropriate. Full details of analysis methods, assumptions, and results will be transparently reported in accordance with the 2022 Consolidated Health Economic Evaluation Reporting Standards (CHEERS 2022) checklist.

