### Data collection and monitoring, study components, and data analysis

Data describing participant demographics and ICU admission will be collected from hospital records and recorded on case report forms (CRFs). Data collected will include date of birth, gender, hospital and ICU length of stay, ICU and hospital survival, ICU readmission rates, mechanical ventilation time, details of their illness, medical treatment, and existing comorbidities. Completed CRFs will be entered into an electronic database. Patient characteristics and ICU admission data will be described using summary statistics. The number of patients approached and consented will be charted, together with the number who dropped out or died.

A data monitoring committee was not considered as this was a low-risk intervention. Data monitoring and study conduct is reviewed 6 monthly by the research investigators and submitted for ethics committee review yearly.

In addition to data from the study components being individually analysed and reported as described below, data analysis will also investigate the relationships between different outcomes/components. Inter-related components that will be explored include whether observed differences in sleep architecture is correlated with changes in delirium outcomes, and whether a difference in the maintenance of circadian rhythm between intervention and control bedspaces impacts the incidence of PICS at 6-month post-ICU discharge.

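### The health-system cost difference counts ICU bed days saved but not ward days, so the estimated saving can be wrong in either direction

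*Protocol article*

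**What the plan says.** Component 7 of the protocol article sets the target broadly: "A within-trial cost-effectiveness analysis will be conducted to estimate the changes to total costs and patient outcomes associated with the intervention". It then says what the cost side is made of. "The change to total costs will reflect the cost of implementing the intervention under different scenarios", and this is "offset by the economic value of ICU bed days saved from reduced ICU length of stay". The perspective follows: "These costs will be measured from the health system perspective".

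Three further statements bear on what is counted:

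- Scenarios: "Planned scenarios will consider different definitions of implementation costs per intervention bedspace". The three definitions are maintaining an existing bedspace (the base case), adding one to an existing ICU, and building a new ICU.
- Sensitivity analysis: "The impact of model input uncertainty on cost-effectiveness outcomes will be examined by deterministic sensitivity analysis and probabilistic sensitivity analysis".
- A separate item: "We will further consider the economic value of lost productivity from the patient perspective".

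The section on data collection and monitoring lists, among the items taken from hospital records for each participant, "hospital and ICU length of stay, ICU and hospital survival, ICU readmission rates, mechanical ventilation time".

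**The concern.** The definition has one added cost (implementation) and one offset (ICU bed days). A patient who leaves the ICU sooner usually goes to a ward bed in the same hospital, and the health system pays for that bed. A cost difference that stops at the ICU door is narrower than its label of total costs and narrower than the stated perspective.

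Nothing else in the section brings ward days in. The scenarios vary implementation cost only. The sensitivity analyses vary the inputs of the model and do not add a missing cost category. Lost productivity is a patient-perspective item.

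The offset matters because the Discussion gives the purpose of the economic evaluation as finding out whether the extra building and technology costs are recovered through better efficiency and outcomes. An error in the offset passes into both the incremental cost-effectiveness ratio and the net monetary benefit.

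**Working it through.** The article states no unit cost and no expected reduction in stay, so there is no figure of its own to reproduce. The check is algebra on the stated definition, with assumed values marked as such.

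**Inputs**

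- From Component 7: added cost = implementation cost; only offset = value of ICU bed days saved; perspective = health system.
- From the data collection section: hospital stay and ICU stay are recorded, so ward days = hospital stay minus ICU stay.
- Assumed: w, the cost of a ward day divided by the cost of an ICU day, at 0.2, 0.3 and 0.4.

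Let D be the mean ICU days saved per patient and H the mean reduction in hospital stay. Ward days then rise by D − H (a fall if H exceeds D). Savings are in units of one gross ICU-day cost.

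**Saving as written**, with the bed day valued gross: D.

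**Saving with ward days counted**: D − w(D − H) = D(1 − w) + wH.

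**Case 1: hospital stay unchanged (H = 0).** The saving is D(1 − w), and the written definition overstates it by 1/(1 − w) − 1.

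- w = 0.2: 1/0.8 − 1 = 25%
- w = 0.3: 1/0.7 − 1 = 43%
- w = 0.4: 1/0.6 − 1 = 67%

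**Case 2: hospital stay falls by exactly the ICU days saved (H = D).** The saving is D(1 − w) + wD = D. The written definition is correct.

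**Case 3: ward stay also shortens (H greater than D).** Take H = 2D as an illustration. The saving is D(1 − w) + 2wD = D(1 + w).

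- w = 0.2: 1/1.2 = 83% of the saving is credited
- w = 0.3: 1/1.3 = 77%
- w = 0.4: 1/1.4 = 71%

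**If the bed-day value is already net of a ward day**, the credited saving is D(1 − w). That is right in Case 1, but it misses wH whenever hospital stay changes. Neither way of valuing the ICU day is right in all three cases. Only counting the ward days is.

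**The case against.** The strongest reply is that this is a condensed article. It says what the cost change will reflect, not that nothing else may enter. It aims at total costs from a health system perspective, promises full reporting to CHEERS 2022, and says that a full protocol is available on request. An itemised list of resources and unit costs commonly sits in such a document, and its absence here would be no fault. That is fair for the list and the prices. It does not remove the point: the article goes beyond silence and names the components of the cost change, and followed as written they leave out ward days. If a fuller plan includes them, the published definition should agree with it.

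A reader might infer three stronger claims, and the document supports none of them.

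- **Every ICU day saved is credited in full.** The value of a bed day is not given and could be set net of a ward day. Full crediting is an assumption, and the overstatement depends on it.
- **Readmissions are never charged.** The article lists ICU length of stay and ICU readmission rates as separate items but does not say whether length of stay covers the first ICU episode or accumulates over the hospital stay. If it accumulates, readmission days are already in the offset, and a separate readmission charge would count them twice.
- **The result is biased towards the upgraded beds.** That holds in Case 1. It reverses if ward stay also shortens.

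The percentages also describe the saving term alone. Their effect on the cost-effectiveness ratio and net monetary benefit depends on implementation cost and quality-adjusted life years, for which the article gives no figures.

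**Conclusion.** The point holds as a mismatch between a stated cost definition and its own label and perspective: ward days are left out although the data to count them are collected. The saving is overstated by 25%, 43% or 67% at assumed ward/ICU cost ratios of 0.2, 0.3 or 0.4, provided that hospital stay is unchanged and the bed-day value is gross. It is understated if ward stay also falls. Neither the direction nor the size of the error in the trial's results can be determined from the article. The matter is confined to the economic component and leaves the clinical comparisons untouched. It is worth correcting before the analysis because the sign and size of the offset are what that component sets out to learn.

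**What to change.** Replace the cost definition in Component 7 with wording to this effect:

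> The change in total costs is the implementation cost plus the between-arm difference in total ICU days and the between-arm difference in ward days, each multiplied by its own gross unit cost. Total ICU days are cumulative over the hospital stay and include readmission days; no separate readmission charge is added. Ward days are hospital stay minus total ICU days. Either difference may be positive or negative.

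Keep the ICU-bed-day-only figure as a secondary scenario, so nothing now planned is lost.

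The cumulative definition matters on both sides. If ICU stay covered only the first episode, readmission days would fall into the remainder and be priced as ward days.

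Cost: a short change of wording and a ward-day unit cost. Hospital and ICU stay are already recorded; the team needs only to confirm that ICU stay is captured, or can be totalled, across readmissions. The downside is that the estimated saving may be less favourable than under the present definition.
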